## Abstract

**Background:**

The cross-sectional area of the subclavian vein (csSCV) is an important factor determining the success rate of SCV catheterization. The head-down position increases the csSCV. However, the effects of lateral tilting on subclavian venous cross-sectional area have not yet been explored. In this trial, we test our hypothesis that ipsilateral tilt during right SCV catheterization may significantly increase the csSCV by impeding blood flow to the heart, thereby increasing the primary venipuncture success rate and reducing the complication rate and procedure time.

**Methods/design:**

This is a two-staged, prospective, randomized, controlled trial conducted on 237 neurosurgical patients requiring SCV catheterization. Seventeen patients in stage I will be placed in supine, 20° ipsilateral tilt, and 20° contralateral tilt positions in random order. The right csSCV will be measured using ultrasonography at each position. In stage II, 220 patients will be randomly assigned to the ipsilateral tilt group (*n* = 110) and supine group (*n* = 110) according to the position for right SCV catheterization. Data on catheterization-related characteristics and complications will be collected during and after catheterization. The primary outcome measures are the right csSCV for stage I and primary venipuncture success rate for stage II. The secondary outcome measures for stage II are time to venipuncture, total catheterization time, first-pass success rate, and complications, such as arterial puncture, hematoma, pneumothorax, air embolism, and catheter misplacement.

**Discussion:**

This is the first trial to investigate the effects of the ipsilateral tilt position on right SCV catheterization. We will attest the beneficial effects of the ipsilateral tilt position on the csSCV and the primary venipuncture success rate during right SCV catheterization. Furthermore, comparisons of the first-pass success rate, complications, and total catheterization time during SCV catheterization in the ipsilateral tilt position vs. the supine position will help us determine which position is better for safe and easy SCV catheterization.

**Trial registration:**

ClinicalTrials.gov, ID: NCT03296735. Registered on 25 September 2017 for stage I; NCT03303274 Registered on 6 October 2017 for stage II.

**Electronic supplementary material:**

The online version of this article (10.1186/s13063-018-2666-8) contains supplementary material, which is available to authorized users.

## Background

Central venous catheterization has been utilized in operating rooms and intensive care units for various purposes, including central venous pressure monitoring, fluid and drug administration, and parenteral nutrition. The internal jugular, subclavian, and femoral veins are used for vascular access. Central venous catheterization through the subclavian vein (SCV) is more comfortable for the patient, with a lower risk for infection but higher risk for pneumothorax compared to femoral and internal jugular venous catheterization [1–3].

The cross-sectional area of the SCV (csSCV) is an important determinant of the success rate of SCV catheterization. Body position can affect the csSCV. Previous studies have shown that the Trendelenburg position increases csSCV [4–7], while contralateral head rotation and placement of a shoulder-roll decreases it [8, 9]. However, the effects of lateral tilt on the csSCV have not been explored. Ipsilateral tilting may expand subclavian venous cross-sectional area by impeding blood flow to the heart, whereas contralateral tilting may reduce the area by venous collapse. Therefore, we hypothesized that the ipsilateral tilt position during right SCV catheterization might significantly increase the csSCV and thereby increase the primary venipuncture success rate and reduce the complication rate and procedure time compared to the supine position.

In this trial, we will compare the right csSCV among supine, ipsilateral tilt, and contralateral tilt positions to determine the beneficial effects of the ipsilateral tilt position on the csSCV, and will assess the venipuncture success rate at the first needling attempt, number of needling attempts for venipuncture, venipuncture time, total catheterization time, first-pass success rate, and complication rate during right-sided SCV catheterization in the supine position vs. the ipsilateral tilt position to determine which position is a better position for safe and easy SCV catheterization.

## Methods

### Study design

This is a two-staged, prospective, single-blind, single-center, superiority, randomized controlled trial. Stage I has a crossover design and stage II has a parallel randomized assignment. This study was approved by the Institutional Review Board of Seoul National University Hospital (number: 1707–110–871, date: 11 September 2017) and registered at ClinicalTrials.gov (NCT03296735 for Stage I and NCT03303274 for stage II). This trial is still being conducted at Seoul National University Hospital. The study protocol is reported according to the Standard Protocol Items: Recommendations for Interventional Trials guidelines (Fig. 1 and Additional file 1). In addition, the final report of this trial will adhere to the Consolidated Standards of Reporting Trials (CONSORT) Statement.

**Fig. 1 Fig1:**
[figure not shown]
Standard Protocol Items: Recommendations for Interventional Trials (SPIRIT) flow diagram: schedule of enrollment, interventions and assessments. *SCV* subclavian vein

### Study population

Adult patients (aged 20–79 years), who are scheduled to undergo elective craniotomy to remove a brain tumor and who require SCV catheterization during the surgery, will be enrolled in this trial. The exclusion criteria are patient refusal; skin infection at the needle puncture site; a known SCV abnormality, such as an anatomical anomaly or thrombus in the SCV; tricuspid valve vegetation; anticoagulant administration; chemoport or pacemaker in situ in the SCV; having undergone right mastectomy or pneumonectomy.

### Ethics, consent, and permission

This study follows the tenets of the Declaration of Helsinki, and written informed consent will be obtained from all participants 1 day before the surgery.

### Withdrawal, dropout, and discontinuation

Participants will be withdrawn from the trial and excluded from the data analysis if they voluntarily withdraw informed consent at any time during the study period. The trial will be discontinued if serious adverse events, such as intractable cardiac arrhythmia, arterial puncture, and evident pneumothorax, and massive air embolism, occur in any patient during the procedure. Any unpredicted adverse events that occurred during the trial will be reported to the Institutional Review Board. The data analyses will be conducted according to the intention-to-treat principle.

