The next 220 patients will be subjected to stage II and randomly placed in either the supine or 20° ipsilateral tilted position for at least 1 min for right SCV catheterization. The head and body will remain neutral in the supine and ipsilateral tilted positions without slight Trendelenburg down. Surgical belts will be tightly strapped around the flanks and knees in the 20° ipsilateral tilted position. In addition, assistants will hold the head and body to prevent an ipsilateral head tilt and the risk of falling down, respectively. No manipulation, including placement of a shoulder-roll or pulling of the ipsilateral arm, will be used for SCV catheterization. After anesthetic induction, the right SCV catheterization will be performed using the Seldinger technique and the anatomical landmark-based method by anesthesiologists who have experienced at least 50 cases of SCV catheterization. The skin area around the right clavicle is disinfected with a solution (72% alcohol plus 2% chlorhexidine). A large, adhesive, disposable drape is aseptically applied to prevent migration of the drape from the procedural field and maintain sterility throughout the procedure. Thereafter, patients are placed in the supine or 20° ipsilateral tilted position for SCV catheterization. The skin puncture point is 1 cm lateral and 1 cm inferior from the inferior border at the mid-point of the clavicle. The skin is punctured with an introducer needle and the needle is advanced towards the SCV for venipuncture. When venipuncture is confirmed with regurgitation of venous blood into the syringe attached to the needle, a guidewire is advanced through the introducer needle. A dilator is advanced through the guidewire and removed to provide easy advancement of a 7 Fr double-lumen central venous catheter (Arrow International Inc., Reading, PA, USA). SCV catheterization is completed when the central venous catheter is inserted at a depth of 13–16 cm, the guidewire is removed, and the indwelling catheter is secured. Patients will receive positive pressure mechanical ventilation before skin puncture with the needle. Mechanical ventilation will be stopped at the time of skin puncture and then resumed after insertion of the indwelling catheter.

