If the first attempt at venipuncture fails, the needle is slowly retreated until the needle tip is in subcutaneous tissue. The angle and depth of the needle will be adjusted for the next needle passage, which is dependent on the practitioner’s judgment. If the first practitioner fails to puncture the SCV after three needling attempts, the second practitioner will attempt venipuncture. If the second practitioner also fails at venipuncture after three needling attempts, the case will be classified as a failed SCV catheterization. In addition, if arterial puncture or air aspiration is evidently detected during the procedure, failure of the SCV catheterization will be considered. In cases of failed SCV catheterization, the central venous catheter will be placed in another central vein, such as the internal jugular or femoral vein.

SCV catheterization-related data, such as the number of needling attempts for venipuncture and total catheterization time, will be collected during the procedure. Clinical signs of air embolism, such as abruptly decreased end tidal carbon dioxide concentration and blood pressure, will be noted. Hematoma, a complication of catheterization, will be detected by the attending anesthesiologists primarily through inspection and manipulation of the puncture site and using ultrasonography if necessary. A chest radiograph will be obtained immediately after surgery to detect catheterization-related complications, such as pneumothorax and misplacement of the catheter tip.

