### Measurements

Demographic data will be collected before SCV catheterization in the stage I patients. The right csSCV will be measured in the supine, 20° ipsilateral tilt, and contralateral tilt positions.

SCV catheterization-related data and demographics will be collected from the stage II patients. The data collected includes the success rate of SCV puncture at the first needling attempt (primary venipuncture success rate), the number of needling attempts for successful venipuncture, venipuncture time (time from skin puncture to venous blood aspiration), total catheterization time (time from skin puncture to completion of indwelling catheter insertion), first-pass success rate of catheterization (success rate of catheterization at the first attempt without any complications and technical disturbances, such as failed venous puncture or difficulties inserting the guidewire, dilator, or catheter), overall success rate of catheterization, the rate of puncture on the anterior wall of the SCV, the incidence of rescue mechanical ventilation, and the number of manipulation attempts to insert the guidewire, dilator, and catheter.

Data on catheterization-related complications, including arterial puncture, hematoma, pneumothorax/hemothorax, air embolism, and misplacement of the catheter tip (placement of the catheter tip in a location other than the superior vena cava or right atrium), will be collected during and after the procedure.

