### Study endpoints

The primary endpoint measures are the csSCV in stage I and the primary venipuncture success rate in stage II. The secondary endpoint measures in stage II are the number of needling attempts for successful venipuncture, venipuncture time, total catheterization time, first-pass success rate, and complication rate.

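### As written, the first arterial puncture in any patient stops the whole trial, yet arterial puncture is a complication the trial plans to count and compare

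*Protocol article*

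**What the plan says.** The stopping rule is one sentence in the protocol article, Methods, under Withdrawal, dropout, and discontinuation: "The trial will be discontinued if serious adverse events, such as intractable cardiac arrhythmia, arterial puncture, and evident pneumothorax", followed by massive air embolism, "occur in any patient during the procedure". It sets no count, rate or review step. The next sentence concerns reporting only: "Any unpredicted adverse events that occurred during the trial will be reported to the Institutional Review Board".

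Four other parts of the article bear on the same event:

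- **Study protocol, size.** "The next 220 patients will be subjected to stage II". The Sample size section asks for at least 100 per group, raised to 110 for dropout.
- **Study protocol, handling of the event.** "if arterial puncture or air aspiration is evidently detected during the procedure, failure of the SCV catheterization will be considered". A failed case then receives a catheter in another central vein.
- **Measurements, Study endpoints and Statistical analysis.** "Data on catheterization-related complications, including arterial puncture, hematoma, pneumothorax/hemothorax, air embolism" are to be collected. The secondary endpoints of stage II include "venipuncture time, total catheterization time, first-pass success rate, and complication rate". The complication rate is tested between groups by the chi-square or Fisher's exact test.
- **Abstract and Discussion.** The abstract names arterial puncture first among the complications. The discussion expects a larger vein to make arterial puncture less frequent.

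**The concern.** The trial treats arterial puncture as something that will happen in some patients and that the tilted position may reduce. A rule that closes the study at the first case does not fit that aim, because a component that can occur at most once cannot be compared between two groups.

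There is a second consequence. If the rule fires early, the primary outcome of stage II, success at the first needling attempt, may be analysed on fewer patients than the sample size calculation requires. If instead the investigators carry on after an arterial puncture, as the procedure section seems to assume, they depart from their own published stopping rule. Either way, the sentence gives the wrong instruction for an event that the rest of the article treats as a patient-level outcome.

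**Working it through.** **Step 1. What the rule acts on.** The object of the sentence is the trial, and the threshold is occurrence in any one patient. The sentence just before it speaks of participants being withdrawn from the trial, so there the word means the study. Arrhythmia, pneumothorax and air embolism each carry a qualifier (intractable, evident, massive). Arterial puncture carries none.

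**Step 2. What the rule does to the comparison.** If the trial stops at the first arterial puncture, the total number observed is 0 or 1. With 1 event and equal groups, the event falls in either group with probability 0.5 under no difference. The two-sided Fisher p-value is then 0.5 + 0.5 = 1, whichever group had the event. This needs no event rate.

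**Step 3. Which complications are affected.**

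| Complication | Trial-level trigger? | Effect on the comparison |
|---|---|---|
| Arterial puncture | Yes, without qualifier | At most one case can be seen |
| Pneumothorax | Only if evident during the procedure | Partial: "A chest radiograph will be obtained immediately after surgery to detect catheterization-related complications, such as pneumothorax", and a case first seen there does not trigger the rule |
| Air embolism | Only if massive | Lesser events can still be counted |
| Hematoma, catheter misplacement | Not listed | None directly |

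**Step 4. The plan's own sample size.** Inputs from the Sample size section are 74.5% in the supine group, an increase of 15% (read as percentage points, so 89.5%), alpha 0.05 (two-sided assumed) and power 80%. With unpooled variance:

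n per group = (0.745 × 0.255 + 0.895 × 0.105) × (1.960 + 0.842)² / 0.15² = 0.28395 × 7.85 / 0.0225 ≈ 99.1, rounded up to 100.

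The pooled formula gives 102 and the arcsine formula 99. The stated 100 per group is reproduced, so 200 evaluable patients is the figure an early stop would undercut.

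**Step 5. Chance that the rule fires in stage II.** The protocol gives no arterial puncture rate, so p is an assumption. For n patients, the chance of at least one event is 1 − (1 − p)ⁿ. The mean number treated up to and including the trigger, capped at 220, is [1 − (1 − p)²²⁰] / p.

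| Assumed p per patient | At least one in 200 | At least one in 220 | Reaches 220 without an event | Mean number treated |
|---|---|---|---|---|
| 0.1% | 18% | 20% | 80% | 198 |
| 0.5% | 63% | 67% | 33% | 134 |
| 1% | 87% | 89% | 11% | 89 |

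An 80% chance of reaching 220 needs p = 1 − 0.8^(1/220), or about 0.10%.

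**The case against.** **It is a slip of wording.** The procedure section is the operative text for this event and ends the attempt in that patient, and the stopping sentence stands under a heading that begins with participant-level matters. This is plausible, and it may well be what was meant. But the sentence says trial, the sentence before it uses that word for the study, and a threshold of any patient makes little sense for one patient's own participation. If patient-level stopping was intended, the sentence still needs the same correction.

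**The word serious limits which punctures count.** Minor punctures could then be collected and compared. The text does not support this well, because arterial puncture is itself given as an example of a serious event, with no severity attached.

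**A planned size and a safety stop often coexist.** This stands. A reader might infer that the rule contradicts the target of 220 patients, or that the trial is bound to stop underpowered. The documents support neither. The conflict with the target is one of feasibility and depends on an event rate that is not given. At 0.1% per patient the trial would finish four times in five.

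**The damage to the endpoint is narrow.** This also stands in part. A reader might infer that the whole complication comparison is lost. It is not, because hematoma, misplacement and pneumothorax found on the later radiograph do not trigger the rule. Nor does the procedure section strictly contradict the stopping rule, since it says nothing about enrolment. It only fits badly with it.

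**Conclusion.** The point holds for arterial puncture, on the text alone. The stopping sentence, followed as written, allows at most one such event, while the abstract and the sections on measurements, endpoints, analysis and discussion plan to count arterial puncture and compare complication rates. This is a stated rule at odds with other stated text, not detail left to a fuller document.

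The risk of stopping short of 100 per group is real but cannot be sized from the protocol. The figures of 20%, 67% and 89% rest on assumed rates of 0.1%, 0.5% and 1%, on independence between patients, and on arterial puncture as the only trigger. For pneumothorax the conflict is partial, and whether a case evident during the procedure should stop the study is a safety judgement. The sentence should be corrected.

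**What to change.** Amend the stopping sentence in three respects:

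- Arterial puncture ends the subclavian attempt in that patient, in line with the procedure section. The patient stays in the allocated group under the intention-to-treat principle and is counted as a complication, and enrolment continues.
- Intractable arrhythmia and massive air embolism remain reasons to stop the trial.
- The investigators and the Institutional Review Board decide whether an evident pneumothorax during the procedure stays a trial-level trigger, and the sentence states the answer.

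No extra patients, procedures or tests are needed. The cost is a small protocol amendment. Because it changes a safety rule in an approved trial that is already recruiting, it needs Institutional Review Board approval.

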### Randomization

The trial follows the CONSORT flow chart from randomization to analysis (Fig. 2). The randomization tables used for stage I and stage II will be prepared before patient enrollment by an anesthesiologist blinded to this trial. An anesthetic nurse who is not involved with the trial will maintain the randomization tables in sealed opaque envelopes. Based on the order of the randomization table, the anesthetic nurse will notify the position sequence in stage I and group allocation in stage II to investigators after eligible patients enter the operating room.

**Fig. 2 Fig2:**
[figure not shown]
Consolidated Standards of Reporting Trials (CONSORT) flow chart

In stage I with a crossover design, the patients will be placed in three different positions (supine, ipsilateral tilt, and contralateral tilt) and the right csSCV will be measured at each position. A random sequence for the three positions is made using the “RAND function” in Excel.

In stage II, patients will be randomly assigned to two groups (supine and ipsilateral tilt groups) with a 1:1 ratio according to the type of position for right SCV catheterization. A random sequence with 4 or 6 random block sizes is created using online random allocation software (http://mahmoodsaghaei.tripod.com/Softwares/randalloc.html).

### Blinding and confidentiality

This is a single-blind trial. Therefore, attending anesthesiologists ([name] and [name]) collecting the data and practitioners performing SCV catheterization are aware of the randomized position order in stage I and the group allocation in stage II.

All patients will be assigned as a study identification number, and the study data will be collected under this number. None of the information that reveals the patient’s identity, including name, social security number, and hospital chart number will be recorded. The data will be kept confidential until the data analyses are completed by the analyzers ([name] and [name]). After study completion, the data will be stored for 3 years and then discarded according to the Korean Enforcement Rule of Bioethics and Safety Act.

### Study protocol

The first 17 patients enrolled in the study will be subjected to stage I, in which the right csSCV will be measured in the supine, 20° ipsilateral tilt, and contralateral tilt positions. After inducing general anesthesia, the patients will be placed in the three different positions based on the order predetermined by the randomized table. The tilted positions will be achieved by tilting the operating tables by 20° ipsilaterally or contralaterally. The patient’s head and body will be placed in a neutral position in the supine as well as in the two tilted positions. Each position will be maintained for 1 min and the right csSCV will be measured using a 4.5–8-MHz linear ultrasound probe (Vscan Extend, GE Healthcare, Seoul, South Korea) at the mid-point of the right clavicle. The SCV is identified by loss of pulsatility, compressibility, and a change in the area corresponding to respiration. An image of the right csSCV will be captured at the end of expiration, and the area will be measured using image-processing software (ImageJ, National Institutes of Health, Bethesda, MD, USA).

The next 220 patients will be subjected to stage II and randomly placed in either the supine or 20° ipsilateral tilted position for at least 1 min for right SCV catheterization. The head and body will remain neutral in the supine and ipsilateral tilted positions without slight Trendelenburg down. Surgical belts will be tightly strapped around the flanks and knees in the 20° ipsilateral tilted position. In addition, assistants will hold the head and body to prevent an ipsilateral head tilt and the risk of falling down, respectively. No manipulation, including placement of a shoulder-roll or pulling of the ipsilateral arm, will be used for SCV catheterization. After anesthetic induction, the right SCV catheterization will be performed using the Seldinger technique and the anatomical landmark-based method by anesthesiologists who have experienced at least 50 cases of SCV catheterization. The skin area around the right clavicle is disinfected with a solution (72% alcohol plus 2% chlorhexidine). A large, adhesive, disposable drape is aseptically applied to prevent migration of the drape from the procedural field and maintain sterility throughout the procedure. Thereafter, patients are placed in the supine or 20° ipsilateral tilted position for SCV catheterization. The skin puncture point is 1 cm lateral and 1 cm inferior from the inferior border at the mid-point of the clavicle. The skin is punctured with an introducer needle and the needle is advanced towards the SCV for venipuncture. When venipuncture is confirmed with regurgitation of venous blood into the syringe attached to the needle, a guidewire is advanced through the introducer needle. A dilator is advanced through the guidewire and removed to provide easy advancement of a 7 Fr double-lumen central venous catheter (Arrow International Inc., Reading, PA, USA). SCV catheterization is completed when the central venous catheter is inserted at a depth of 13–16 cm, the guidewire is removed, and the indwelling catheter is secured. Patients will receive positive pressure mechanical ventilation before skin puncture with the needle. Mechanical ventilation will be stopped at the time of skin puncture and then resumed after insertion of the indwelling catheter.

If the first attempt at venipuncture fails, the needle is slowly retreated until the needle tip is in subcutaneous tissue. The angle and depth of the needle will be adjusted for the next needle passage, which is dependent on the practitioner’s judgment. If the first practitioner fails to puncture the SCV after three needling attempts, the second practitioner will attempt venipuncture. If the second practitioner also fails at venipuncture after three needling attempts, the case will be classified as a failed SCV catheterization. In addition, if arterial puncture or air aspiration is evidently detected during the procedure, failure of the SCV catheterization will be considered. In cases of failed SCV catheterization, the central venous catheter will be placed in another central vein, such as the internal jugular or femoral vein.

SCV catheterization-related data, such as the number of needling attempts for venipuncture and total catheterization time, will be collected during the procedure. Clinical signs of air embolism, such as abruptly decreased end tidal carbon dioxide concentration and blood pressure, will be noted. Hematoma, a complication of catheterization, will be detected by the attending anesthesiologists primarily through inspection and manipulation of the puncture site and using ultrasonography if necessary. A chest radiograph will be obtained immediately after surgery to detect catheterization-related complications, such as pneumothorax and misplacement of the catheter tip.

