### Sample size

The right csSCV in the supine position for stage I was reported to be 0.93 ± 0.17 cm^2^ in a previous study [10]. At an alpha level of 0.017 and a beta level of 0.2, a minimum of 15 patients are required to confirm a 15% increase in the csSCV in the ipsilateral tilt position compared to the supine position in the same patient. Considering a 10% dropout rate, 17 patients are needed for stage I.

In stage II, the primary venipuncture success rate has been reported to be 74.5% in the supine position during right SCV catheterization [11]. At the alpha level of 0.05 and a beta level of 0.2, at least 100 patients per group are needed to determine a 15% increase in primary venipuncture success rate in the ipsilateral tilt position. Assuming a 10% dropout rate, 110 patients are needed in each group.

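### Stage I describes one ultrasound image per position for its primary endpoint; averaging three would cheaply reduce random measurement error in a 17-patient paired comparison.

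*Protocol article*

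**What the plan says.** The cross-sectional area of the right subclavian vein (csSCV) is the stage I primary endpoint (Study endpoints: "The primary endpoint measures are the csSCV in stage I and the primary venipuncture success rate in stage II").

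The Study protocol section sets out how it is obtained. The device and site are a "4.5–8-MHz linear ultrasound probe (Vscan Extend, GE Healthcare, Seoul, South Korea) at the mid-point of the right clavicle". On timing it says "Each position will be maintained for 1 min", and on capture and reading, "An image of the right csSCV will be captured at the end of expiration, and the area will be measured using image-processing software". The same section identifies the vein partly by its compressibility and by the change in its area with breathing. Nowhere does the article mention a second capture, an average, a second reading or a repeatability figure.

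The Sample size section takes its input from an earlier study ("The right csSCV in the supine position for stage I was reported to be 0.93 ± 0.17 cm^2^ in a previous study") and concludes: "At an alpha level of 0.017 and a beta level of 0.2, a minimum of 15 patients are required". A 10% dropout allowance brings this to 17. The Statistical analysis section compares positions with paired t or Wilcoxon signed-rank tests at 0.017 (0.05/3).

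**The concern.** By the article's own description, the measured area depends on how hard the probe presses and on the moment in the breathing cycle. One traced frame also carries error from probe angle and outlining. In a paired design, stable differences between patients cancel but image error does not: each difference contains the error of two images.

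The planned effect is small in absolute terms, 15% of 0.93 cm², or about 0.14 cm², and is tested in 17 patients at a strict alpha. Precision in each area therefore matters, and replication buys precision without recruiting anyone. With one image per position, measurement error also cannot be separated from true within-patient variation, so the trial could not report how repeatable its primary measurement is.

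**Working it through.** **Inputs from the Sample size and Statistical analysis sections.** Supine mean 0.93 cm², SD 0.17 cm², increase 15%, alpha 0.017 (0.05/3), power 0.80, minimum n = 15, n = 17 with dropout.

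**Assumptions not in the documents.** Two-sided testing; SD of the paired difference (SD_diff) = 0.17 cm²; share f of the difference variance that is independent image error.

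**1. The plan's own figure.** The effect is 0.15 × 0.93 = 0.1395 cm². The article gives no SD for a paired difference. Using the supine SD for it implies a within-patient correlation of 0.5, because SD_diff = 0.17 × √(2(1 − ρ)) = 0.17 at ρ = 0.5. Then

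n = ((z₀.₉₉₁₅ + z₀.₈₀) × SD_diff / effect)² = ((2.387 + 0.842) × 0.17 / 0.1395)² = 15.48,

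which rounds up to 16, one more than the stated 15. Dropout: 15 / 0.90 = 16.7, so 17, as stated.

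**2. Power with one image.** With the noncentral t distribution (paired test, two-sided, alpha 0.05/3), power is 67.6% at n = 15 and 75.2% at n = 17.

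**3. What averaging removes.** The mean of k captures with independent errors has 1/k of the single-image error variance.

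| Captures | Error variance removed | Fall in error SD |
|---|---|---|
| 2 | 50% | 29% |
| 3 | 67% | 42% |
| 5 | 80% | 55% |

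**4. Power with three captures averaged.** If a single image has error SD σₑ, the difference carries 2σₑ², so f = 2σₑ² / 0.17². After averaging three, SD_diff = 0.17 × √(1 − f + f/3).

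| f | Implied single-image error SD (cm²; % of 0.93) | SD_diff, three averaged (cm²) | Power, n = 15 | Power, n = 17 |
|---|---|---|---|---|
| 0 | 0 | 0.170 | 67.6% | 75.2% |
| 0.05 | 0.027 (2.9%) | 0.167 | 69.3% | 76.9% |
| 0.10 | 0.038 (4.1%) | 0.164 | 71.0% | 78.5% |
| 0.20 | 0.054 (5.8%) | 0.158 | 74.7% | 81.8% |
| 0.30 | 0.066 (7.1%) | 0.152 | 78.5% | 85.1% |
| 0.50 | 0.085 (9.1%) | 0.139 | 86.2% | 91.4% |

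The f = 0 row is also the one-image power for every f, because 0.17 is taken to include the image error already.

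**5. Sensitivity to the assumed SD_diff.** One-image power at n = 17 is 58% for a within-patient correlation of 0.3 (SD_diff 0.201), 75% for 0.5, 85% for 0.6 (0.152) and 94% for 0.7 (0.132).

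**The case against.** **The text may be condensed.** The evidence for a single capture is the singular wording of one sentence, and a journal article may leave replicate details to the full protocol. This has some force. But the section fixes probe frequency, device, site, hold time, respiratory phase and software, and describes one image at the end of that chain. Read as written, that is a stated method that can be improved.

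**Much is already standardised.** Site, end-expiration, time in position, tilt angle and neutral posture are fixed, under general anaesthesia. This stands and limits the error, respiratory timing included. It does not fix probe pressure, angle or outlining.

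**The gain may be small.** No passage gives an error size. At f = 0.05 to 0.10 the gain is only about 2 to 3 percentage points. The 75% baseline is itself an assumption, as step 5 shows. Both stand.

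**Stronger readings that the documents do not support:**
- *That stage I is underpowered because of single capture.* The shortfall from 80% in step 2 arises because a normal approximation is set against an exact t calculation at an assumed SD_diff. The cited 0.17 is also an observed SD that already contains the earlier study's measurement error.
- *That averaging would remove most of the measurement error.* It acts only on independent error. A probe angle kept across captures, a tracing habit, or influence from data collectors who know the position order (Blinding and confidentiality) would remain.
- *That random image error biases the result or endangers stage II.* Random error costs precision and does not shift the paired mean. The article makes entry to stage II depend on no stage I result. The sample size also covers only ipsilateral tilt versus supine, not all three contrasts.

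**Conclusion.** The point holds as a modest matter of precision. The article describes one image per position for a primary endpoint measured on a compressible vein, with no repeatability check, in a small paired comparison. Three averaged captures would be a better method for the same patients.

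The secure part of the size is the reduction in independent error: two-thirds of its variance, or 42% of its SD. The effect on power is conditional. With SD_diff 0.17 cm² and two-sided testing, it runs from about 2 points (f = 0.05) to about 16 points (f = 0.50) at n = 17, and nothing in the documents says where in that range the trial lies. The article contains no contradiction or arithmetic error on this point, and the stated sample size is not shown to be wrong by it. It is worth considering as a cheap improvement, at low priority.

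**What to change.** In the Study protocol section, state that in each position, after the 1-minute hold, three end-expiratory images are captured on separate breaths, with the probe lifted and replaced between captures. Trace each image and use the mean area as the patient's csSCV for that position. Report the within-position repeatability SD with the stage I results. Replacing the probe matters: without it, placement and pressure error is shared by the three images and does not average out.

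If the full protocol already specifies repeat captures, stating their number and how they are combined is enough.

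Cost: two extra images in each of three positions, six per patient, so 17 × 6 = 102 more tracings. Time in each position is slightly longer, equally across positions. No additional patients are needed. The change does not address assessor knowledge of the position.
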